## Abstract

**Background:**

Chronic obstructive pulmonary disease (COPD) is a widespread chronic illness that affects millions of people around the world. Its management not only necessitates medical intervention but also long-term patient self-management. Most traditional self-management education fails to address individualized needs and ongoing support. With improvements in information technology, especially in the application of artificial intelligence (AI) for health management, new avenues have emerged that can improve COPD patients’ self-management capacity, ultimately leading to better disease control and improved quality of life. Thus, we have developed an AI Health Education Accurately Linking System (AI-HEALS) to examine if AI-HEALS-based intervention is effective in enhancing COPD patients’ ability for self-management, ultimately leading to better disease management and improved quality of life.

**Methods and analysis:**

This randomized controlled trial (RCT) aims to evaluate the efficacy of AI-HEALS intervention implemented through WeChat platform in improving self-management ability of COPD patients. Eligible COPD patients meeting the inclusion criteria will be randomly assigned to either an intervention group or a control group. The control group will receive standard treatment, while the intervention group will receive the AI-HEALS program in addition to standard treatment. The AI-HEALS system is an AI driven question and answer platform with integrated voice interaction capabilities, designed to facilitate easier interaction between patients and the system. It provides real-time physiological monitoring, medication and behavior reminders, and personalized health education through the “COPD Health Management Expert” WeChat platform. The system is supported by a self-developed knowledge base based on established clinical guidelines and evidence for COPD, ensuring the accuracy and reliability of the information provided. Outcome measurements will be conducted at multiple time points, including baseline (upon enrollment), hospital discharge, the end of the intervention, and at 3, 6, and 9 months after the completion of the intervention.

**Ethics and dissemination:**

Ethical approval for the study was obtained from the Medical Ethics Committee of Zigong First People’s Hospital [Ethics No. Ethics (Research) 2024, Issue 152, 31/10/2024]. The clinical trial is registered under ChiCTR2400092829, with registration completed on 25/11/2024.

**Study Protocol Registration:**

[https://www.chictr.org.cn/bin/home], identifier [ChiCTR2400092829].

## Introduction

1

Chronic obstructive pulmonary disease (COPD) is one of the most common respiratory disorders, primarily characterized by progressive airflow limitation, which may be accompanied by inflammatory lung diseases (1, 2). COPD is highly prevalent globally, with a global prevalence of 10.3% (95% CI 8.2–12.8) among people aged 30–79 years in 2019, based on GOLD case definitions, according to the results of a systematic review (3). The major risk factors for COPD include long-term smoking, air pollution, occupational exposures, and genetic predisposition (4). COPD not only has a profound impact on individual health, leading to persistent dyspnea, fatigue, and frequent respiratory infections, but it also imposes a substantial burden on families and society (5). For example, disease exacerbations often result in a decline in the patient’s ability to work, increasing the caregiving burden on family members (5). Additionally, frequent hospital visits and long-term medical expenses place considerable strain on healthcare systems (6).

Currently, the treatment of COPD primarily relies on pharmacological therapy, rehabilitation training, and patient education (1, 2). Pharmacological treatment mainly includes long-acting β2-agonists, long-acting muscarinic antagonists, and corticosteroids (7). These medications help alleviate symptoms, improve lung function, and reduce the frequency of acute exacerbations (7). Additionally, pulmonary rehabilitation, which includes aerobic exercise, strength training, and breathing techniques, has been shown to enhance patients’ exercise tolerance and quality of life (8). Patient education, on the other hand, aims to increase patients’ understanding of the disease and improve their self-management abilities, thereby enhancing symptom control.

Although these traditional interventions have been somewhat effective, they exhibit several notable limitations. First, their reliance on face-to-face interactions and in-person treatment settings has resulted in unequal distribution of healthcare resources and limited access to medical care, particularly in low-resource and remote areas (9). Moreover, medication adherence and long-term maintenance pose additional challenges. Many patients may interrupt their treatment due to side effects, cost concerns, or misunderstandings about the effectiveness of the therapy. Furthermore, low participation rates in pulmonary rehabilitation are a common issue, with many patients lacking motivation to engage in rehabilitation programs, or facing barriers such as limited facilities or trained personnel (10). Lastly, existing patient education often overlooks the integration of mental health support and behavioral health, which are crucial for promoting health behavior change and managing COPD in the long term (11).

In recent years, mobile health interventions have also demonstrated significant potential in the management of COPD. A systematic review by Zangger et al., which included 130 randomized controlled trials, demonstrated that digital health interventions significantly improve objective measures of physical activity and function in COPD patients compared to traditional care (12). These interventions also resulted in improvements in depression, anxiety, and health-related quality of life (12). Additionally, a study by Zanaboni et al., involving the random allocation of 120 participants, found that remote rehabilitation and unsupervised training effectively reduced the incidence of hospitalizations and emergency visits, while significantly improving health status and exercise capacity over the course of 1 year (13). Further confirming these findings, Wang et al. showed that interventions delivered via mobile health applications not only significantly improved scores on COPD Assessment Tests and self-management scales over a 12-months period, but also promoted exercise and smoking cessation behaviors in patients (14). However, despite these encouraging findings, there are still certain limitations to current mHealth solutions for COPD that need to be addressed. Currently, mHealth solutions for COPD are largely based on standardized and rule-based designs, which are not very adaptable to individual variations and needs. Indeed, current mHealth solutions for COPD are largely unidimensional, focusing only on specific aspects such as exercise encouragement or monitoring of symptoms, and do not provide comprehensive mHealth solutions for long-term self-management of these patients. Additionally, since current mHealth solutions do not make use of intelligent data analysis and active decision-making, they are not very effective at making timely and personalized interventions to these patients.

In today’s social arena, application of the Artificial Intelligence Health Education Accurately Linking System (AI-HEALS), an artificial intelligence-based health education system on WeChat, the largest social media in China, is especially significant. AI-HEALS uses economical and ubiquitous mobile communication technology, which enables patients to easily obtain ongoing disease care and management from home. Interventions in AI-HEALS are based on the integrative Health Behavior Promotion Model (HAPA-MTM), which not only supports physical symptoms management in patients but also focuses on mental health and behavior change, ultimately providing an all-encompassing and long-term management approach (15, 16). Its main features involve AI-based Q&A based on an in-house knowledge database, physiological indicator tracking and behavior monitoring, various reminder services, and customized information delivery. This new intervention model is more adaptable to cater to health management requirements of contemporary society, with an effective support and management solution for COPD patient population, and demonstrating the potential of emerging technology in health management.

In summary, this study proposes to assess the efficacy of AI-HEALS intervention in managing one’s own health in COPD patients by conducting a randomized controlled trial (RCT), with special emphasis on the following:

Evaluate the efficacy of a 3-months intervention program based on the AI-HEALS in enhancing physiological markers in COPD patients;Assessing the efficacy of a 3-months multidisciplinary intervention program based on AI-HEALS to improve psychological markers among COPD patients;Assess the efficacy of a 3-months multifaceted intervention program based on the AI-HEALS to enhance self-management behaviors among COPD patients.

## Materials and methods

2

### Design

2.1

It is a single-blind, parallel-controlled, randomized study in which patients diagnosed with COPD from a general public hospital in Zigong, China, participated. This is a single-center study. The study design and grouping are presented in Figure 1.

**FIGURE 1 F1:**
[figure not shown]
Flow chart of patient recruitment and study implementation. Eligible patients with chronic obstructive pulmonary disease are screened and randomized in a 1:1 ratio to the intervention or control group. Baseline assessments are conducted prior to the intervention. The intervention group receives a 3-months AI-HEALS–based program in addition to standard treatment, while the control group receives standard treatment alone.

### Randomization and blinding

2.2

In this research, a computer-generated random number sequence will be applied in randomization. Patients will be assigned to intervention and standard care groups in a 1:1 ratio. Randomization will be carried out prior to their hospital admission. Through this process, every patient will be assigned to their corresponding study group based on a predetermined sequence to ensure randomness and equity of allocation. Upon entering their ward, each patient will receive a unique code that is equivalent to the random number sequence for facilitation of smooth and uninterrupted recruitment. Once randomization is completed, patients will be transferred to their respective ward depending on their assigned groups. Specifically, intervention patients will be admitted to Ward A, with patients in the control arm going to Ward B to avoid possible cross-contamination between different treatments.

In order to maintain confidentiality of sequence allocation, an independent team member not involved in participant registration or in intervening in any way in the allocation process will perform randomization. This step aims to avoid revealing the randomization sequence during the study. The allocation outcome will then be communicated by the independent team member to the intervention team so that neither the participant registration team nor intervention team knows beforehand against which group a participant is registered.

Finally, due to the novelty of this AI-HEALS intervention therapy in this trial, full participant and therapist blinding is not possible. This limitation might lead to some type of biases, such as performance bias due to participants’ knowledge of their treatment allocation, or detection bias due to knowledge by therapists of implemented treatments. To mitigate these biases, we will take a series of steps to mitigate their effects on the study. Firstly, participant names of all intervention and control groups will be kept anonymous until study completion. Secondly, an independent study staff member who does not take part in participant registration or intervention delivery will be responsible for conducting the random allocation. This individual will forward the allocation results to the intervention team directly to prevent both the enrollment team and intervention team from knowing group assignments beforehand. Thirdly, intervention group patients will be admitted to Ward A, while patients in the control group will stay in Ward B, to avoid any cross-contamination between intervention and control groups. Lastly, to further decrease bias, study data will be collected by research assistants without knowledge of their group allocations. Further, during the analysis process, no knowledge of group allocations will exist for data analysts. During conducting the study, data will be coded and kept confidential to preserve the integrity of blinding.

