### Recruitment

2.5

This study aims at enrolling participants who qualify for inclusion and exclusion in the target hospital. Recruitment will be performed by the medical staff of the hospital, which will screen eligible patients upon their discharge or admitting them to extend their invites. Next, an initial personal contact with patients will be made by the research team, whose study’s purpose, procedures involved, probable gains, and possible risks will be explained in details. Eligible patients will be invited to their respective hospitals for a comprehensive health evaluation, which includes an in-depth review of the history of COPD, and symptoms. Upon ensuring that patients understand the study completely by answering their questions, participants will be asked to sign an approved consent document. Participants that have signed an approved consent document will be officially enrolled in a study. Apart from this, we will use a consistent measurement proxy to make sure that measurements by self-report are reliable.

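### Randomisation before admission (2.2) does not fit recruitment at discharge (2.5), and the article nowhere places consent and baseline CAT before allocation

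*Protocol article*

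**What the plan says.** **Randomisation and wards.** Section 2.2 states: "Randomization will be carried out prior to their hospital admission". The arm then decides the ward: "intervention patients will be admitted to Ward A, with patients in the control arm going to Ward B". On entering the ward each patient receives a code tied to the random sequence. Section 2.2 adds that an independent team member performs the randomisation and that the registration and intervention teams do not know assignments in advance.

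**Recruitment and consent.** Section 2.5 gives recruitment to hospital staff, described as those "which will screen eligible patients upon their discharge or admitting them to extend their invites". Explanation of the study, a health evaluation and consent come next, and "Participants that have signed an approved consent document will be officially enrolled in a study".

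**Baseline.** The abstract lists the measurement times as "including baseline (upon enrollment), hospital discharge, the end of the intervention". The Figure 1 caption says "Eligible patients with chronic obstructive pulmonary disease are screened and randomized in a 1:1 ratio" and, on baseline, only that "Baseline assessments are conducted prior to the intervention".

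**Table 1 and the outcome.** Table 1 puts eligibility screen, consent, allocation and baseline CAT in one column at time 0, with discharge as a later, separate assessment. Section 2.8.1 makes the change in CAT the primary outcome, measured at baseline, discharge and after the intervention.

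**The concern.** Section 2.2 starts from randomisation and ends in a ward that identifies the arm. Section 2.5 starts from a patient who is being admitted or discharged and ends in consent. Joined as written, allocation and ward placement come first, and consent and baseline CAT come after.

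Three things would then be at stake:

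- **Who enters.** Patients could accept or refuse, and staff could include or exclude, with the arm in view.
- **The baseline.** CAT is completed by the patient, and the article concedes that participants cannot be blinded. A baseline given with knowledge of the arm enters the primary outcome directly, because that outcome is a change score.
- **What the pilot passes on.** Section 2.4 uses the pilot's effect size to size the main trial, so a distorted estimate would carry forward.

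**Working it through.** No figure in the plan bears on the order of events, so the check is a comparison of the stated steps, followed by an illustration of size.

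**1. Order of events, by source**

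| Source | What it fixes | What it leaves open |
|---|---|---|
| Section 2.2 | Randomisation before admission; ward by arm afterwards | Whether consent and baseline are already done |
| Section 2.5 | Screening at admission or discharge, then evaluation, consent, enrolment | Where randomisation falls |
| Abstract | Baseline upon enrolment, so after consent | Baseline relative to allocation |
| Figure 1 caption | Screening, then randomisation; baseline before the intervention | Consent, and baseline relative to randomisation |
| Table 1 | All entry steps at time 0; discharge later | Order within time 0 |

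**2. Discharge route.** The patient is first screened when leaving hospital. Consent, enrolment and hence baseline fall at or after that moment. Randomisation before that admission, and placement in Ward A or B for that stay, are then impossible without randomising someone not yet screened or consented. The baseline CAT also cannot precede the discharge CAT, although Table 1 and section 2.8.1 treat them as two successive measurements.

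**3. Admission route.** Screening, consent, baseline and randomisation could all take place just before ward entry. That order satisfies sections 2.2 and 2.5, the caption and Table 1. It is nowhere written down. If randomisation and ward placement come first, the ward can show the arm to patient and recruiter before consent and baseline CAT.

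**4. Illustration of size.** Assume a normal outcome with SD 1, and that the worst fraction p is lost from one arm only. The mean of that arm moves by φ(z_p)/(1 − p), where φ is the standard normal density and z_p cuts off the upper fraction p.

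- p = 0.10: 0.1755 / 0.90 = 0.195 SD
- p = 0.20: 0.2800 / 0.80 = 0.350 SD

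Section 2.4 aims at about 25 per group, so the standard error of the standardised difference is √(2/25) = 0.283. The shifts are 0.195/0.283 = 0.69 and 0.350/0.283 = 1.24 standard errors.

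The values of p are assumptions; the article gives no rate of refusal or exclusion by arm. If patients are lost according to baseline severity, the mean of the change in CAT moves only by the above shift times the correlation between baseline and change. The figures are therefore a ceiling for each p.

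**The case against.** **A workable order exists and several places point to it.** The Figure 1 caption puts screening before randomisation. Table 1 lists screening, consent and allocation in that row order. Inclusion criterion 5 requires signed consent before the study starts. Section 2.5 invites patients to hospital for an evaluation, which fits someone not yet on a ward. All of this stands for the admission route, so a claim that sections 2.2 and 2.5 can never be reconciled would go too far. But row order within one time column is not a stated sequence, and none of these places says where the baseline CAT falls relative to allocation. Nor do they rescue recruitment at discharge. Screening at one discharge could serve a later admission, but section 2.5 does not describe that.

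**There are safeguards.** An independent person randomises, teams are not told in advance, and data collectors are said to be unaware of allocation. This protects the sequence before assignment. It does not hide an assignment that the ward already shows, and it does not blind the patient who fills in the CAT.

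**Stronger inferences.** A reader might infer that patients and recruiters will know the arm before consent. The text shows only that they can, if the steps run in the order written. A reader might also infer that Figure 1 places baseline after randomisation. Only the caption is available, and it is silent on that point. Finally, a reader might infer that the intention-to-treat set is limited to consenting patients. Section 2.11 says only that intention to treat will be followed, and the definition of the set may stand in an analysis plan not shown.

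**Conclusion.** The point holds as an unresolved contradiction in the sequence of entry steps. Recruitment at discharge from the same stay is incompatible with randomisation before admission, with arm-specific wards for that stay, and with separate baseline and discharge CAT assessments. For recruitment at admission the text permits a sound order but does not fix it: no place in the article puts consent and the self-reported baseline CAT before allocation.

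The consequence is a possible loss of concealment, with arm-dependent consent or exclusion and a baseline influenced by knowledge of the arm. Its size cannot be derived from the article. The range of 0.7 to 1.2 standard errors should not be read as an expected bias: it assumes perfectly selective loss of 10% to 20% from one arm only, in a phase whose stated primary objective is not hypothesis testing. The contradiction does not depend on that range. It should be settled before enrolment, because a baseline taken after the arm is known cannot be repaired in the analysis.

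**What to change.** State one order in sections 2.2 and 2.5, the Figure 1 caption and Table 1:

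1. screening;
2. consent;
3. baseline questionnaires, including CAT;
4. release of the assignment by the independent team member;
5. placement in Ward A or Ward B.

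In section 2.2, replace the pre-admission timing with: *after consent and baseline assessment and before ward placement*. Ward placement has to be named. If patients are recruited in hospital without it, they are already on some ward before assignment.

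In section 2.5, remove recruitment at discharge from the same stay, so that the baseline CAT always precedes the discharge CAT. State that intention to treat applies to everyone for whom an assignment was released.

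The cost is wording and a fixed order of steps at entry, with no extra patients. The downside is that consent and baseline must be finished before ward placement, which may slow admission slightly.

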### Study sample

2.3

All patients diagnosed with COPD are eligible to participate in the study. Additionally, participants must meet the following criteria:

#### Inclusion criteria

2.3.1

(1) Age ≥ 18 years; (2) Diagnosis of COPD according to the GOLD (Global Initiative for Chronic Obstructive Lung Disease) criteria; (3) No acute disease exacerbations or any severe health conditions over the past month, ensuring stability of disease status over the intervention duration; (4) Proficiency in operating a smartphone and use of WeChat on a regular basis, to facilitate easy participation in WeChat-based intervention program; (5) Being willing to take part in the study and sign an informed consent agreement before starting the study.

#### Exclusion criteria

2.3.2

(1) Severe mental illness or cognitive impairment that hinders collaboration with the researchers; (2) Inability to operate a smartphone; (3) Prior involvement in similar studies.

#### Withdrawal criteria

2.3.3

(1) Individuals withdraw from participation in the study due to personal reasons such as scheduling conflicts or change of interest; (2) Development of severe adverse effects in relation to study participation, including acute event (for example, myocardial infarction, severe infection) or severe illness that necessitates suspension of intervention; (3) Alteration in participant status or medical advice that requires adjustment of the initial treatment regimen, which would be in conflict with study intervention.

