### Informed consent

2.6

The process of informed consent will be done openly and transparently, adhering strictly to ethics. Participants meeting inclusion and exclusion criteria will be given a detailed written document describing the aims of the study, procedures, possible hazards and gains, and measures for protecting their information. It also includes explicit details of their information being collected, stored, and secured. We will keep all data securely encrypted on secured servers, accessible only by authorized members of our research team during the study, and properly disposed of after study completion. Participants will have sufficient time to read carefully through the consent document, request any questions, and provide consent voluntarily. Participants will be clearly informed that they can withdraw from the study at any point without any adverse consequences. We will offer continuous points of contact for consultations so that participants can seek additional information or clarifications if required. During the study, we will make all new information available to participants that could change their decision to remain in the study, ensuring continuous informed consent.

In addition, individuals who withdraw from the intervention group will not be penalized. Where intervention is underway, patients who withdraw cannot be reassigned to the control arm and will be counted as a natural attrition case. Semi-structured interviews with patients who withdraw, where possible, will be conducted to learn about their reasons for withdrawal. Participants will be made explicitly informed of all possible options upon withdrawal at the point of informed consent, so that they are aware of their rights and choices at all times.

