### Statistical analysis

2.11

We will collect quantitative data using a structured questionnaire and then input it into Microsoft Excel for analysis. All major analyses will follow intention to treat (ITT) and will undergo protocol compliant (PP) analysis for sensitivity testing. Descriptive statistics will be used to summarize feasibility variables such as starting information, number of participants, and system usage. For continuous data, the mean and standard deviation of normally distributed data, as well as the median and 25th to 75th percentile of non-parametric data, will be provided. To compare the untreated group and the group measured once, independent sample *t*-tests and their non-parametric analogues will be used. The categorical data will be expressed in frequency and percentage, and analyzed using chi square test. The normality of the data will be tested using the Kolmogorov Smirnov test. Under the assumption of random missing data, established multiple imputation methods will be used in appropriate circumstances to handle the missing data. We will examine and compare the missing and wear patterns between each group to identify potential differences in dropout rates, and conduct sensitivity analysis to compare estimated and complete case outcomes. For the main experiments, the focus will be on using a linear mixed effects model to evaluate the main outcome indicators. For secondary outcomes such as self-management and psychosocial/cognitive outcomes, analysis will use similar mixed effects models or simpler comparison methods, depending on the nature and timing of data collection. In addition, exploratory age stratification analysis can be conducted to examine the potential heterogeneity of intervention effects across different age groups in a descriptive manner. Given the pilot nature of the study, the results should be interpreted with caution. The measurement criteria used by the system, such as the number of questions, will be summarized in a descriptive manner and can be included as covariates in exploratory analysis to better understand compliance patterns; these analyses will be seen as hypothesis generation rather than validation. All statistical tests are two-sided, with a significance level of 0.05. Data analysis will be conducted using IBM SPSS Statistics (version 24.0; SPSS Inc., Chicago, Illinois, USA and Stata (version 14.0); StataCorp, College Station, TX, The United States) conducted.

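### The withdrawal criteria do not separate stopping AI-HEALS from leaving follow-up, which risks differential, outcome-related loss of CAT data that the planned checks would not detect

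*Protocol article*

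**What the plan says.** Section 2.3.3 of the protocol article gives three withdrawal criteria in one list. The first is a personal decision to leave the study. The second is a severe adverse effect related to taking part, described as including an "acute event (for example, myocardial infarction, severe infection) or severe illness that necessitates suspension of intervention". The third is "Alteration in participant status or medical advice that requires adjustment of the initial treatment regimen, which would be in conflict with study intervention".

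Section 2.6 says of the intervention group that "patients who withdraw cannot be reassigned to the control arm and will be counted as a natural attrition case".

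Section 2.11 plans that "All major analyses will follow intention to treat (ITT) and will undergo protocol compliant (PP) analysis for sensitivity testing". The primary outcome is to be analysed with a linear mixed model. On missing data it says: "Under the assumption of random missing data, established multiple imputation methods will be used in appropriate circumstances to handle the missing data". It adds a comparison of missingness between the groups and a comparison of imputed with complete-case results.

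Section 2.8.1 makes change in CAT the primary outcome, measured at baseline, discharge and the end of the 3-month intervention. Section 2.8.2 lists 30-day readmission as a secondary outcome. It also plans to collect dropout rates and reasons and to compare the characteristics and outcomes of those who drop out. Section 2.9 plans contact after discharge by WeChat, telephone or text message.

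**The concern.** Criteria 2 and 3 describe reasons to interrupt the intervention, yet they stand as reasons to withdraw, beside a criterion that plainly means leaving the study. Site staff who follow the list can reasonably stop collecting data when either criterion is met. The article has no statement to prevent this.

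Two features make such loss awkward. First, the triggers are clinical events or changes of treatment, which plausibly go with a worse CAT and with readmission, both of which the trial measures. Second, they are tied to the study intervention. A control patient, who under section 2.7.1 has no access to AI-HEALS, has nothing to suspend and nothing for a new regimen to conflict with. Two patients with the same clinical course could therefore be handled differently by arm.

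If post-event CAT scores are lost mainly in the intervention arm and imputed from patients who stayed, the comparison shifts towards AI-HEALS. Scores that were never collected cannot be recovered at analysis. Section 2.4 then carries the pilot's effect size and variance into the design of the main trial.

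**Working it through.** **1. The plan's own figure.** Section 2.4 wants about 25 evaluable patients per group (50 in total), expects 10% to 20% attrition and recruits 60 (30 per group).
- 50 / (1 − 0.10) = 55.6, rounded up to 56
- 50 / (1 − 0.20) = 62.5, rounded up to 63
- 50 × 1.20 = 60
- Attrition implied by 25 of 30: 1 − 25/30 = 16.7%

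The target of 60 agrees with the stated range and is not in question. At 10% to 20%, 3 to 6 of 30 patients per arm are lost, leaving 27 to 24.

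**2. What the sections say about a patient who meets criterion 2 or 3.**
- Does data collection stop? Section 2.3.3 does not say so, but it classes the patient as withdrawn.
- Does data collection continue? No section says so.
- Is the patient removed from the ITT set? No section says so.
- Does the attrition sentence in section 2.6 apply? It is written for patients who withdraw from the intervention group; extending it to criteria 2 and 3 is an inference.

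**3. Whether the planned checks would reveal outcome-related loss.** A mixed model or imputation can condition on CAT already observed at baseline and discharge, and loss explained by those values is still missing at random. An event after discharge that both triggers withdrawal and worsens the next, uncollected CAT is not captured that way. Complete-case and per-protocol analyses rest on assumptions at least as strong. Comparing dropouts uses only what was observed before they left. None of these tests the case at issue.

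**4. Illustrative size.** The documents give no CAT standard deviation, no withdrawal rate by reason and no split by arm. Assume that lost patients in both arms have a true CAT δ points worse than imputed. Then

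bias = (loss in intervention − loss in control) × δ.

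| Loss, intervention vs control | δ = 2 | δ = 4 | δ = 8 |
|---|---|---|---|
| 20% vs 10% | 0.2 | 0.4 | 0.8 |
| 20% vs 20% | 0 | 0 | 0 |
| 10% vs 20% | −0.2 | −0.4 | −0.8 |

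Positive values favour AI-HEALS.

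**5. Carry-forward.** With the standard deviation held fixed, the required N is proportional to 1/effect². If the pilot estimate equals the true effect plus the bias, the main trial gets (true / (true + bias))² of the N it needs.
- Assumed true effect of 2 points, bias 0.2, 0.4, 0.8: (2/2.2)² = 83%, (2/2.4)² = 69%, (2/2.8)² = 51%
- Assumed true effect of 4 points, same biases: (4/4.2)² = 91%, (4/4.4)² = 83%, (4/4.8)² = 69%

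Both true effects are assumptions; the article states none.

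**The case against.** A reader might infer more than the text supports, and the trial team could fairly reject four such readings.

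- **That section 2.3.3 contradicts ITT.** It does not. No sentence excludes withdrawn patients from the analysis set, and a mixed model with multiple imputation can keep everyone randomised in the analysis. What is missing is an assurance that their outcomes will be observed.
- **That patients are removed for any acute illness.** Criterion 2 is limited to effects related to study participation, and criterion 3 to changes that conflict with the intervention. AI-HEALS is described as education and self-management support only, so a routine regimen change need not conflict with it.
- **That all such patients are written off as attrition.** Section 2.6 sits within informed consent and concerns patients who withdraw from the intervention group.
- **That the whole 10% to 20% attrition can be charged to one arm.** With a shift of 3 to 6 points this would give 0.10 × 3 = 0.3 to 0.20 × 6 = 1.2 points. But the attrition figure covers every reason, including personal ones, and is not split by arm, and the shift has no source in the article.

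The trial team can add that the primary endpoint is reached at the end of a 3-month intervention, that entrants must have been stable over the past month, that dropout is already to be described, and that the pilot does not aim at hypothesis testing.

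All of this stands and lowers the severity. It does not remove the point. Who remains in follow-up is a rule of conduct that the article itself sets, not a detail left to an analysis plan, and section 2.11 itself names the missingness assumption and the checks on it. The pilot label does not help either, since its estimates are meant to size the main trial.

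**Conclusion.** The point holds as a weakness of moderate severity, not as a must-fix. Section 2.3.3 fails to separate stopping the intervention from leaving the study, its clinical criteria bear mainly on the AI-HEALS arm, and the planned analyses would not show whether the resulting loss depends on outcome. Differential, outcome-related loss is a plausible risk; the documents do not establish that it will happen.

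The size cannot be derived from the article. The 0.2 to 0.8 CAT points rest on two assumptions: loss of 20% against 10%, and lost patients 2 to 8 points worse than imputed. Equal loss with an equal shift gives no bias, and heavier loss among controls would reverse its direction.

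**What to change.** 1. Leave the clinical triggers in section 2.3.3 as they are; nothing here judges them.
2. State in section 2.3.3 that meeting criterion 2 or 3 bears on exposure to the intervention and does not end follow-up, in either arm, unless the patient withdraws consent.
3. Continue scheduled CAT assessments and readmission recording for these patients, using the contact already planned in section 2.9.
4. Record the reason for stopping, by arm.
5. Confirm in section 2.11 that all patients are analysed as randomised. Beside the complete-case comparison, add a delta-adjusted (missing-not-at-random) sensitivity analysis in which imputed CAT after stopping is made worse by a range of amounts, including different amounts by arm.

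The cost is a rewording of two sections, a few more follow-up contacts and one more analysis. The recruitment target of 60 does not change. The wording should be settled before patients meet these criteria, because scores that are not collected cannot be replaced.
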